## 4.0 TREATMENT PLAN (For approximate timing of treatments see appendix 6)

---

Prior to commencing treatment patients who are current smokers should be advised of the benefits of stopping smoking, and should be offered any available support to quit. Stopping smoking is associated with a reduction in the risk of radiation induced side effects and in some patients also results in improved survival

### 4.1 CHEMOTHERAPY

Patients should start chemotherapy within two weeks of randomisation and within two weeks of a clinical assessment of fitness (section 4.1.1). Chemotherapy is cisplatin and etoposide and is given for 4 to 6 cycles. One cycle is given prior to radiotherapy. The second cycle in both arms is given concurrently with radiotherapy if possible. Radiotherapy will start on day 22 of cycle 1. In the BD radiotherapy arm, the third to sixth cycles (if applicable) are given after completion of the thoracic radiotherapy. In OD radiotherapy arm, the third & fourth cycles of PE are also given concurrently and the fifth & sixth cycles (if applicable) are given after completion of the thoracic radiotherapy.

Centres will be given the choice to stop chemotherapy after 4 cycles or to continue to up to 6 cycles. Centres who decide to give 6 cycles will have to continue doing so for all patients entered in the trial (unless it is decided that it is not in the patients best interest to receive cycle 5 and 6 or due to patient's choice)

#### 4.1.1 Clinical assessments (see section 6.5)

Assessments should be repeated as necessary, and are required prior to each chemotherapy cycle:

- Clinical examination
- Assessment of performance status (see appendix 1), 'dyspnoea score' (see appendix 3) and toxicity
- FBC, U&Es and LFTs:
  - Bone marrow reserve should be adequate for chemotherapy (i.e. absolute neutrophil count  $> 1.5 \times 10^9/l$  and platelet count  $> 100 \times 10^9/l$ )
  - Biochemistry
- Assessment of renal function:
  - Adequate renal function - defined by  $GFR \geq 50$  ml/min (measured by EDTA). The Cockcroft and Gault formula (see appendix 5) may be used to estimate GFR, but if  $< 50$  ml/min then EDTA should be performed.
- Disease status – a CXR will be done prior to cycle 1, 3 and 5 (if 6 cycles of chemotherapy are given). If a CXR shows suspicion of progressive disease a CT scan thorax and abdomen should be done to confirm progression before stopping chemotherapy. A formal assessment with repeat CT scan should be made within 4 weeks after completion of the concurrent chemoradiotherapy.

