### Duration of assessment

Patients will be assessed prior to each cycle of chemotherapy and at 4 weeks after the final cycle. Follow-up will be at 3 monthly intervals for 12 months and six monthly thereafter until death. Post treatment CT scans thorax and abdomen will be done within 4 weeks of cycle 4 (even if 6 cycles are given) and 6 months after randomisation.

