### **4.3 TWICE DAILY THORACIC RADIOTHERAPY**

#### **4.3.1 Schedule**

- **45 Gy in 30 twice daily fractions** over a period of **19 days** (radiotherapy to start on a Monday), 5 consecutive days a week
- The optimal overall treatment time should be 19 days, up to 21 days is a protocol deviation and should be recorded, above 21 days is a protocol violation.
- The interfraction interval will be 6 to 8 hours.
- using conformal radiotherapy and 4 to 10 MV photons emitted from linear accelerators.

- Thoracic radiotherapy will start on cycle 1 day 22, if possible concurrently with the second cycle of chemotherapy (within 24 hours of day 1, cycle 2 of PE).
- Concurrent chemotherapy will be administered during the intervals between the 2 daily radiotherapy fractions.

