### **6.2 ASSESSMENTS AT FOLLOW-UP**

After completion of treatment, patients should be reviewed weekly until acute side effects have resolved then 3 monthly until 1 year, 6 monthly thereafter.

Follow up visits at more frequent intervals should be undertaken at the discretion of the participating clinician.

Assessments to include:

- Clinical examination, performance status (see appendix 1), dyspnoea score (see appendix 3) and weight
- Assessment of any continuing or new toxicity (see appendix 2)
- Assessment of disease status
- Assessment of response by a contrasted CT scan thorax and abdomen within 4 weeks of cycle 4 (even if 6 cycles are given), 6 months after randomisation and 12 months after randomisation.
- Details of any additional cancer treatment received
- Late toxicity (CTCAE v3.0)

Participating sites should make all necessary efforts to ensure that follow-up information is obtained for all participants e.g. this may include methods such as tracking the patient through a national cancer registry, GP records network etc if contact is lost.

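### Section 4.1.1 and section 6.2 time the post-treatment CT differently: on planned timings the two rules nearly coincide in the once-daily arm but set deadlines 24–26 days apart in the twice-daily arm

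*Supplement*

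**What the plan says.** In the latest protocol version, section 4.1.1 ends its list of pre-cycle checks with: "A formal assessment with repeat CT scan should be made within 4 weeks after completion of the concurrent chemoradiotherapy".

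Section 6.2 places the response CT "within 4 weeks of cycle 4 (even if 6 cycles are given), 6 months after randomisation and 12 months after randomisation". The Summary, under Duration of assessment, uses the same anchor: "within 4 weeks of cycle 4 (even if 6 cycles are given) and 6 months after randomisation". The visit table in section 6.4 shows one end-of-treatment CT, after cycle 4, and further scans at 6 and 12 months from randomisation.

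The response analysis in protocol section 7.3.2, repeated in the SAP, takes best response up to roughly 28 days after cycle 4 in both arms (or after the last cycle, if chemotherapy stopped earlier). It compares the arms with chi-squared and Fisher tests. Neither document says which scans count.

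Which cycles are concurrent depends on the arm. Section 4.1 states: "In the BD radiotherapy arm, the third to sixth cycles (if applicable) are given after completion of the thoracic radiotherapy". In the OD arm, cycles 2, 3 and 4 all overlap with radiotherapy.

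**The concern.** The two rules use different clocks. The cycle-4 clock is the same in both arms. The end of concurrent chemoradiotherapy is set by the radiotherapy schedule, which is what was randomised, so a scan timed from it falls at a different point in each arm.

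If a BD site adds the 4.1.1 scan to the cycle-4 scan, its patients have two opportunities to record a response before the cut-off, while OD patients normally have one. If it uses the 4.1.1 scan instead, BD response may be read after two or three cycles and OD response after four. An extra early scan could also lower the reference sum from which later progression is judged, because Appendix 4 measures progression against the smallest sum recorded since treatment began. The two radiotherapy schedules are plainly visible to sites and no masked reading of these scans is described, so an avoidable difference in timing between arms is worth removing.

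**Working it through.** **Inputs**

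- Radiotherapy start, both arms (section 4.1): "Radiotherapy will start on day 22 of cycle 1".
- BD overall time (section 4.3.1): "The optimal overall treatment time should be 19 days". OD overall time (section 4.4.1): 45 days.
- Cycle interval (section 4.1.2): 21 days, with etoposide on days 1–3.
- Scan allowance: 4 weeks = 28 days under either rule.

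**Reproducing the plan's treatment times** (Monday start, five treatment days a week)

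- BD: 30 fractions ÷ 2 per day = 15 treatment days = three Monday-to-Friday weeks. 2 × 7 + 5 = 19 days, which agrees.
- OD: 33 treatment days = six full weeks plus three days. 6 × 7 + 3 = 45 days, which agrees.
- Difference: 45 − 19 = 26 days.

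**End of concurrent treatment**

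- BD: 22 + 19 − 1 = day 40.
- OD: 22 + 45 − 1 = day 66.

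**Cycle 4**

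- Day 1 of cycle 4 = 1 + 3 × 21 = day 64. Last dose, two days later, is day 66.
- In the OD arm, cycle 4 and radiotherapy therefore finish on the same day.

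**Scan windows**

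| | Section 4.1.1 | Cycle-4 rule | Gap between deadlines |
|---|---|---|---|
| BD | days 40–68 (40 + 28) | to day 92 (64 + 28) or 94 (66 + 28) | 92 − 68 = 24, to 94 − 68 = 26 |
| OD | days 66–94 (66 + 28) | to day 92 or 94 | 0 to 2 |

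The two entries for the cycle-4 rule depend on whether the four weeks run from the first or the last day of the cycle. In the BD arm the windows share only about days 64–68. In the OD arm they are practically the same window, so one scan meets both rules.

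**Cycles given before a BD scan under 4.1.1**

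Cycle starts fall on days 1, 22, 43 and 64. A scan on days 40–42 follows two cycles, and one on days 43–63 follows the start of the third. Only from day 64 has the fourth begun.

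**With the cycle-4 anchor in both arms**

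The deadline is day 92–94 in each arm, so the planned difference is 0 days instead of 26.

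**The case against.** A reader might infer that response and local progression are in fact assessed on an arm-dependent schedule, with two scans for every BD patient and one for every OD patient. The documents do not support that. The Summary, section 6.2, the visit table and both statements of the response analysis use the cycle-4 anchor, and the visit table shows only one post-treatment CT before 6 months. The outlier is one sentence. A BD site can also meet both rules with a single scan on about days 64–68. These points stand, so the asymmetry is a possibility at sites that act on 4.1.1 and not a property of the design.

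It can also be argued that concurrent chemoradiotherapy in 4.1.1 names the whole regimen, since the Rationale uses a similar phrase as a label for it. With four cycles the rules would then agree in both arms. The wording allows this, but section 4.1, just before, separates cycles given with radiotherapy from those given after it, so day 40 is the plainer reading for BD. Nor does the other reading remove the conflict at six-cycle centres. Cycle 6 would end on day 1 + 5 × 21 + 2 = 108 and the CT would be due by day 108 + 28 = 136, against day 92–94 in section 6.2, although the gap would then be equal in both arms.

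The consequences are limited too:

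- Response is analysed but is absent from the primary and secondary endpoints in sections 2.1 and 7.1.1.
- Where the cycle-4 scan is also done, an extra early scan alters best response only for a patient who responds early and has lost that response by cycle 4. The documents give no rate for this.
- Local progression-free survival dates progression from the earliest clinical evidence. Chest X-rays before cycles 3 and 5 (the latter with six cycles), and CT on suspicion, apply to both arms. The 6- and 12-month CTs run from randomisation. One early scan is all that can differ, and 26 days separates deadlines, not actual scan dates.

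**Conclusion.** The inconsistency is real and needs reconciling. It bites in the BD arm only, where the 4.1.1 deadline (day 68) precedes the cycle-4 deadline (day 92–94) by 24–26 days. In the OD arm the rules differ by at most 2 days. Where sites follow 4.1.1, BD patients could be scanned earlier, or once more, than OD patients before the response cut-off.

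The comparison chiefly exposed is response. The effect on local progression-free survival is limited and on overall survival nil. The material does not allow a bias in either comparison to be quantified, and none is claimed.

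The day counts assume treatment on schedule, full cycles without delay, a post-treatment CT taken after cycle 4 begins, and 4.1.1 read as the end of radiotherapy with its concurrent cycles.

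Separately, the Summary stops at the 6-month CT, whereas section 6.2 and the visit table also require one at 12 months. This affects both arms alike and is editorial.

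**What to change.** Reconcile the sentence in section 4.1.1 with the Summary, section 6.2 and the table in section 6.4, so that the scheduled post-treatment CT used for response is tied to cycle 4 in both arms. If a separate scan at the end of radiotherapy is intended, the table and section 6.2 should say so, and the analysis should state how it enters best response. Leave CT for suspected progression unchanged. Add the 12-month CT to the Summary.

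Limiting best response to scheduled scans in the SAP is a further option but is debatable, because Appendix 4 counts the best response recorded from the start of treatment. It is not needed once the anchor is common.

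The cost is one sentence in section 4.1.1 and one phrase in the Summary. Aligning to cycle 4 requires no additional scans.

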#### 4.1.2 Chemotherapy Administration

The chemotherapy doses should be based on the patient's calculated pre-treatment body surface area using actual body weight. A detailed plan for administering a cycle of chemotherapy including suggested hydration and anti emetics is given in appendix 6.

**In summary**, centres can opt for one of the two chemotherapy regimen. Cycles are given at 3 weeks intervals:

- Etoposide  $100 \text{ mg/m}^2$  iv D1-3  
Cisplatin  $75 \text{ mg/m}^2$  iv D1
- Or**
- Etoposide  $100 \text{ mg/m}^2$  iv D1-3  
Cisplatin  $25 \text{ mg/m}^2$  iv D1-3

Patients should be encouraged to take a high oral fluid intake on the day prior to cisplatin chemotherapy.

#### 4.1.3 Dose modifications

The policy should be to delay and give at full dose, rather than reduced dose. The dose modification schedule should be followed, but clinical judgement should be used in individual cases. Common side effects are listed in appendices 7 & 8.

#### ***Haematological toxicity***

Dose modifications are based on each pre-treatment blood count.

| ANC x 10  /l                                                |     | Platelets x 10  /l                                                                      | Cisplatin /Etoposide                                                                                                                                                  |
|-------------------------------------------------------------------------|-----|-----------------------------------------------------------------------------------------------------|-----------------------------------------------------------------------------------------------------------------------------------------------------------------------|
| > 1.5                                                                   | And | >100                                                                                                | Full dose                                                                                                                                                             |
| ≤ 1.5                                                                   | Or  | ≤ 100                                                                                               | Delay until recovery                                                                                                                                                  |
| Febrile neutropenia or treatment delay for grade 4 neutropenia > 7 days | Or  | Grade 4 platelets requiring medical intervention or ≥ grade 2 bleeding with thrombocytopenia | First event: full dose and GCSF support (see paragraph 4.6) is recommended or 20% dose reduction
Second event: 30% dose reduction
Third event: off trial |

- If chemotherapy cannot be administered after a three-week delay because of haematological toxicity, chemotherapy should be discontinued.
- Use of GCSF see paragraph 4.6
- If Hb<10 a blood transfusion will be required

#### ***Non-haematological toxicity***

##### **Hepatic toxicity**

| AST/ALT   |     | Bilirubin   | Cisplatin                                                                                  | Etoposide |
|-----------|-----|-------------|--------------------------------------------------------------------------------------------|-----------|
| 2-5 x ULN | and | < 1.5 x ULN | Full dose                                                                                  | Full dose |
| >5 x ULN  | or  | >1.5 x ULN  | Delay one week then reassess using the same criteria; if delayed for two weeks discontinue |           |

##### **Renal toxicity**

- Request GFR (*EDTA clearance*) before each course of chemotherapy ***If*** creatinine clearance < 50 ml/min
- If GFR re-estimated please dose according to the table:

| GFR              | Cisplatin                                               | Etoposide          |
|------------------|---------------------------------------------------------|--------------------|
| $\geq 50$ ml/min | Full dose                                               | Full dose          |
| 40-49 ml/min     | 50% dose reduction or substitute with carboplatin AUC 5 | 20% dose reduction |
| < 40 ml/min      | Off trial                                               | Off trial          |

**Other toxicities** (see appendix 2)

|                                                        |                                                                                                                       |
|--------------------------------------------------------|-----------------------------------------------------------------------------------------------------------------------|
| Peripheral neuropathy $\geq$ grade 2                   | Substitute carboplatin AUC 5 or 50% cisplatin dose reduction after recovery to $\leq$ grade 1; 100% dose of etoposide |
| Any grade 3-4 toxicities except mucocitis and alopecia | 25% dose reduction for cisplatin and etoposide after recovery to $\leq$ grade 1                                       |

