#### **4.7 CRITERIA FOR STOPPING TREATMENT**

Protocol treatment may be stopped in the following instances:

- Evidence of progressive disease according to RECIST criteria on CT scan (appendix 4)
- Unacceptable toxicity
- An early toxicity assessment (after 20 patients have completed treatment in each arm) for safety reasons will be carried out. Data will be reviewed by the TMG.
- Intercurrent illness which, in the clinician's opinion, would require discontinuation of protocol therapy.
- If subsequent histological/cytological review is contrary to the original diagnosis
- Patient's request

For patients with measurable disease, evidence of minor disease progression (stable disease by RECIST criteria) is not a requirement to stop treatment in an otherwise clinically and symptomatically stable patient.

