| Vomiting                                                                                                                                                   | Vomiting                                             | 1 episode in 24 hrs                                                | 2-5 episodes in 24 hrs. IV fluids for <24 hrs                                                                       | ≥ 6 episodes in 24 hrs or IV fluids or TPN ≥ 24 hrs                                                                                  | Life threatening consequences                                                  | Death |
| Infection                                                                                                                                                  |                                                      |                                                                    |                                                                                                                     |                                                                                                                                      |                                                                                |       |
| Febrile neutropenia (fever of unknown origin without clinically or microbiologically documented infection (ANC <1.0 x 10  /L, fever ≥ 38.5 °C) | Febrile neutropenia                                  | -                                                                  | -                                                                                                                   | Present                                                                                                                              | Life threatening consequences eg septic shock, hypotension, acidosis, necrosis | Death |
| Infection (documented clinically or microbiologically) with Grade 3 or 4 neutrophils (ANC <1.0 x 10  /L)
- Select                    | Infection (documented clinically)
- Select | -                                                                  | Localized, local intervention indicated                                                                             | IV antibiotic, antifungal or antiviral interventional or operative intervention                                                      | Life threatening consequences eg septic shock, hypotension, acidosis, necrosis | Death |

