| Myelitis                                           | Myelitis                                                                            | Asymptomatic, mild signs eg
Babinski's or L'Hermite's sign                                                         | Weakness or sensory loss not
interfering with ADL                                                                        | Weakness or sensory loss
interfering with ADL                    | Disabling                   | Death |
| Neuropathy: sensory                                | Neuropathy: sensory                                                                 | Asymptomatic; loss of deep
tendon reflexes or parasthesia
(including tingling) not
interfering with function | Sensory alteration of paresthesia
(including tingling), interfering
with function, but not interfering
but not ADL | Sensory alteration or parasthesia
interfering with ADL           | Disabling                   | Death |
| Somnolence/
Depressed level of
consciousness | Somnolence                                                                          | -                                                                                                                     | Somnolence or sedation
interfering with function, but not
with ADL                                                    | Obtundation or stupor, difficult
to arouse, interfering with ADL | Coma                        | Death |
| Pain -select                                       |                                                                                     |                                                                                                                       |                                                                                                                             |                                                                     |                             |       |
| Pain
- Select                                   | - Pulmonary/
Upper respiratory
- Select
- Chest wall
- Chest/thorax NOS | Mild pain not interfering with
function                                                                            | Moderate pain; pain or
analgesics interfering with
function, but not interfering with
ADL                          | Severe pain; pain or analgesics
severely interfering with ADL    | Disabling                   | -     |

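### Grade 3–4 peripheral neuropathy meets two conflicting rows of the dose-modification table, and the protocol does not say which one governs

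*Supplement*

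**What the plan says.** The latest protocol version closes its dose-modification rules (section 4.1.3) with a two-row table headed Other toxicities, which refers the reader to Appendix 2 for grading.

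- **Neuropathy row.** The trigger is peripheral neuropathy of grade 2 or above, with no upper limit. The action is "Substitute carboplatin AUC 5 or 50% cisplatin dose reduction after recovery" to grade 1 or less, with etoposide kept at 100%.
- **Catch-all row.** The trigger is "Any grade 3-4 toxicities except mucocitis and alopecia". The action is "25% dose reduction for cisplatin and etoposide after recovery" to grade 1 or less.

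The general instruction at the head of section 4.1.3 is "The dose modification schedule should be followed, but clinical judgement should be used in individual cases". It also prefers delay at full dose to dose reduction. Nothing in section 4.1.3, or in the carboplatin dosing paragraph that follows (4.1.4), says which row applies when a patient meets both.

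**The concern.** Appendix 2 grades sensory neuropathy up to grade 4. Grade 3 begins "Sensory alteration or parasthesia" and requires interference with daily activities; grade 4 is disabling. A patient at either grade satisfies both triggers, and the two actions differ for both drugs. Taking the lower dose of each drug does not resolve this, because the neuropathy row explicitly keeps etoposide at 100%.

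The direction of the conflict matters. Under the catch-all row, more severe neuropathy leads to more cisplatin than the neuropathy row allows at grade 2. Appendix 7 describes the neurotoxicity of cisplatin as mainly peripheral neuropathy and warns that it can worsen even once the drug is stopped. At stake is the safety of individual patients who continue treatment, not the trial's comparison.

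**Working it through.** The plan states no figure of its own here, so the check sets the two rows side by side and works out the doses.

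**Inputs.** Cisplatin is 75 mg/m² on day 1, or 25 mg/m² on each of days 1–3. Etoposide is 100 mg/m² on each of days 1–3, that is 3 × 100 = 300 mg/m² per cycle (section 4.1.2 and Appendix 6). The reductions are those of the two rows in section 4.1.3.

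**Next cycle after grade 3–4 neuropathy, recovered to grade 1 or less:**

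| | Neuropathy row | Catch-all row | Catch-all minus neuropathy row |
|---|---|---|---|
| Cisplatin, day 1 regimen (mg/m²) | 75 × 0.50 = 37.5 | 75 × 0.75 = 56.25 | +18.75 |
| Cisplatin, split regimen (mg/m² per day) | 25 × 0.50 = 12.5 | 25 × 0.75 = 18.75 | +6.25 |
| Etoposide (mg/m² per cycle) | 300 × 1.00 = 300 | 300 × 0.75 = 225 | −75 |

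- The cisplatin ratio is 56.25 / 37.5 = 1.5.
- The excess is 18.75 / 75 = 25% of the planned cisplatin dose. The split regimen gives the same total per cycle, 3 × 6.25 = 18.75 mg/m².
- If the clinician takes the carboplatin option in the neuropathy row, the cisplatin contrast is 56.25 against 0 mg/m².

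**Can the catch-all be read as fully literal?** No. Appendix 2 lists "Febrile neutropenia (fever of unknown origin without clinically or microbiologically documented infection" only from grade 3 upwards, so a literal catch-all would cover it too. The haematological table gives it a different rule: "First event: full dose and GCSF support (see paragraph 4.6) is recommended", or a 20% reduction; then 30% at the second event. So at least one named toxicity in section 4.1.3 follows its own rule. That rule, however, is in a separate table. The two rows at issue are adjacent in one table, and the catch-all lists its exceptions without naming neuropathy.

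**Effect on the dose-intensity endpoint.** Section 7.5 weights the two drugs equally. The dose term for the affected cycle is ½(0.50 + 1.00) = 0.75 under the neuropathy row with reduced cisplatin, and ½(0.75 + 0.75) = 0.75 under the catch-all. The summary is the same for either choice unless carboplatin is substituted.

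**How many patients?** The documents give no frequency of grade 3–4 neuropathy, nor of recovery to grade 1 or less while cycles remain. No count can be derived.

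**The case against.** The strongest reply is that the specific row governs the general one. The neuropathy trigger is written as grade 2 or worse, which expressly brings in grades 3 and 4; if the catch-all took over at grade 3, the row need only have said grade 2. Mucositis and alopecia had to be excepted because they have no dose row of their own, whereas neuropathy has one directly above. Febrile neutropenia shows the same convention. A clinician is unlikely to give 75% cisplatin after grade 3–4 neuropathy when the row above gives 50% or carboplatin at grade 2.

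There are further safeguards. Section 4.1.3 allows clinical judgement, and section 4.7 allows treatment to stop for "Unacceptable toxicity". Appendix 7 says recovery can take a year or longer, while cycles are three-weekly and number four to six, so few patients may ever reach the catch-all dose. The rule is the same in both arms.

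Most of this stands. The specific row is the likely reading and the practical effect is small. But the protocol does not state that reading, and a list of exceptions that omits neuropathy invites the other one. Slow recovery does not remove the conflict entirely either: the recovery condition in the neuropathy row can be read as attaching only to the cisplatin option. On that reading an unrecovered patient could move to carboplatin with full etoposide, while the catch-all would require recovery first.

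**Conclusion.** The point holds as a minor dosing-safety error in the wording. Two stated rules apply to the same patient and cannot both be obeyed, and the one that names neuropathy only by failing to except it gives the less cautious cisplatin dose. The size per affected cycle is 18.75 mg/m² more cisplatin (1.5 times) and 75 mg/m² less etoposide, assuming the catch-all row is followed literally and the comparison is with the reduced-cisplatin option.

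Those are the consequences of one reading of the table, not expected effects across the trial; the number of patients could be close to nil. The sample size and the primary survival analysis are unaffected. Any such dose would be visible in the data, because Form A (section 6.5) records treatment received and the reasons for reductions, and section 7.10 summarises reductions by arm.

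**What to change.** Reword the trigger of the catch-all row so that its exceptions are mucositis, alopecia and peripheral neuropathy, with a pointer to the row above for the last. Leave the neuropathy row as it is, including the choice between carboplatin AUC 5 and 50% cisplatin. Tell sites by a short memo.

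The cost is a few words in one table row and the memo. No extra data, visits or patients are needed.
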